### Follow-Up Assessments

At both 6 weeks and 6 months postpartum, all participants in both groups will be sent a text message asking them to complete a follow-up survey. Participants will be asked to provide consent, and once consent is given, they will start the survey. Participants who complete the follow-up surveys will receive an electronic gift card worth Can $15 (US $11.97) for each survey. To remind participants to complete the survey, reminder text messages will be sent via TextIt every other day for 2 weeks (a maximum of 6 total messages) or until the survey is completed. An email will be sent as a final reminder to participants who have not yet completed the survey after day 14. If an email address was not provided, an expanded text message will be sent on day 14 instead.

### Blinding

Because of the nature of the Essential Coaching for Every Mother program, blinding of participants is not possible, and therefore participants will be informed of their group allocation. To minimize personnel blinding related to data collection, no hospital staff will be informed of participants’ involvement in the study. This is possible because Essential Coaching for Every Mother is sent to the participant’s personal cell phone, with no in-person component to the intervention. The lead researcher will be aware of participants’ allocations and will be responsible for summarizing data but will not be involved in the randomization procedure, which will occur directly in the TextIt platform. Additionally, there will be no interaction between the participants and anyone on the research team because everything occurs remotely via a previously set up process, reducing any risk of personnel or outcome assessor bias.

### Sample Size

The sample size was calculated based on the primary outcome of self-efficacy using the findings from our feasibility study [24], which showed a mean difference in self-efficacy scores between baseline and 6-week follow-up of 3.78 (SD 4.5). Therefore, with stratification by parity and a moderate intraclass correlation of ρ=0.2, a sample size of 30 participants per cluster and 60 participants per group (120 total participants) is required to be powered for analysis at the level of parity. In the feasibility study, there was an incompletion rate of 15.5%; thus, the estimated sample size will be increased by 15% to 69 participants per group, rounded up to 70 participants. In total, 140 participants will be enrolled in the study.

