While postpartum mobile apps are also growing in prevalence, a recent systematic review identified 48 mobile apps of varying quality [14]. Also, mobile apps require access to data plans, rely on push notifications that may not be enabled, and are time consuming to build. On the other hand, one aspect of mHealth that shows significant promise is text messaging because of its cost-effectiveness, broad reach, and simplicity of use. There is some evidence that text messaging programs can enhance maternal and newborn outcomes and engage mothers during the postnatal period [15,16]. Existing postpartum text message programs focus on various postpartum topics—text4baby aims to improve perinatal health for women and their infants [17], MobileMums is focused on enhancing physical activity [18], and MumBubConnect’s goal is to promote breastfeeding [19]—yet no postpartum text message programs are currently available in Canada. The provision of timely health information can influence behaviors through repeated and relevant health messages [20]. Text messages can be sent, saved, and retrieved at any time [21], are able to be personalized and tailored, and can be provided through one- or two-way communication [22]. Therefore, a text message program was designed with low barriers to entry, low cost for participation, and ease of development and modification.

Our team developed Essential Coaching for Every Mother, an evidence-based postpartum text message program, with the goal of improving mothers’ access to information about caring for themselves and their newborn during the immediate 6-week period after birth [23]. The program was developed through iterative testing with mothers and postpartum health care providers [23] and showed preliminary effectiveness and uptake during a pilot pre-post intervention study offered during COVID-19 [24].

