### Data Analysis

Data will be analyzed on an intention-to-treat basis (excluding women who requested to stop receiving the messages or were lost to follow-up). Demographic characteristics on maternal age, marital status, education level, and delivery method will be expressed as means and standard deviations or percentages, as applicable, based on group allocation. Postnatal contacts for themselves and their infants, health concerns, and feeding behavior will also be expressed as means and standard deviations or percentages, as applicable, based on group allocation. Any significant differences in baseline characteristics, examined through a chi-square analysis or Mann-Whitney test, will be adjusted for in the analysis. A *P* value of 0.05 will be considered significant for all outcomes.

For the primary outcome of self-efficacy, a total score will be reported using means, standard deviations, and percentages. Analysis of covariance (ANCOVA) will be used to measure whether total self-efficacy scores differ between the 2 groups, with adjustments for the pretest scores and any significant baseline characteristics.

For the first secondary objective, an ANCOVA will be used to determine whether scores differ between the 2 groups on social support, postpartum anxiety, and postpartum depression, with adjustments for the pretest scores and any significant baseline characteristics. For the second secondary objective, a 2-way ANCOVA will be used to measure whether the mean difference of self-efficacy scores differs between the 4 groups (multiparous/primiparous and intervention/control), with adjustments for any significant covariates on self-efficacy, social support, postpartum anxiety, and postpartum depression. For the third secondary objective, a 2-way repeated-measures ANCOVA will be used to explore whether changes in the key psychosocial outcome variables varied over time.

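### The sample size treats an uncontrolled before-after change as the between-arm effect and cites a cluster ICC that does not apply, so the parity-level power claim lacks support

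*Protocol article*

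**What the plan says.** Protocol article, Sample Size: the calculation is for self-efficacy and uses the feasibility study, which "showed a mean difference in self-efficacy scores between baseline and 6-week follow-up of 3.78 (SD 4.5". Background says that the program "showed preliminary effectiveness and uptake during a pilot pre-post intervention study offered during COVID-19"; no comparison group is mentioned.

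Sample Size then states that "with stratification by parity and a moderate intraclass correlation of ρ=0.2, a sample size of 30 participants per cluster and 60 participants per group" are needed, and that this size "is required to be powered for analysis at the level of parity". It gives no power percentage, no sidedness and no between-arm difference. Data Analysis sets the significance level: a P "value of 0.05 will be considered significant for all outcomes".

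Other sections fix what the calculation has to serve:

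- Randomization allocates individual participants 1:1 after sorting them into two parity strata.
- Data Analysis compares the two arms on self-efficacy by ANCOVA adjusted for the pretest score, and examines parity by a 2-way ANCOVA across the four parity-by-arm cells.
- Effectiveness Objectives asks whether the effect varies with parity, and Effectiveness Hypotheses predicts that it does not.

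**The concern.** Three things do not fit together.

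1. **The effect.** A before-after change in a single group contains whatever change usual-care mothers would also show over the same six weeks. That part cancels when the arms are compared, so 3.78 is a different quantity from the one the primary analysis estimates.
2. **The ICC.** Parity is a two-level stratification factor. No groups of women are randomized, so a cluster inflation has no place in this design.
3. **The parity claim.** The text says that the trial is powered for analysis by parity. It does not say whether that means the arm comparison inside each stratum or the comparison of effects between strata. The objective is the second, which needs far more women.

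At stake is how a null result is read. A non-significant parity interaction would appear to confirm the stated hypothesis of no difference when the trial may have had little chance of finding one. A null overall result could be read against a planning effect that was never a between-arm effect.

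**Working it through.** **Inputs.** From Sample Size: change 3.78, SD 4.5, ICC 0.2, 30 per cell, 60 per group. From Data Analysis: alpha 0.05. Assumed, because not stated: two-sided testing, and power of 80% or 90%. Powers are normal approximations unless marked (t).

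**1. Reproducing the stated size.** Treat 3.78 as a between-arm difference, with no ICC:

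n per arm = 2 × (z for alpha + z for power)² × (SD/difference)²

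- 90% power: 2 × (1.960 + 1.2816)² × (4.5/3.78)² = 29.8, so 30
- 80% power: 2 × (1.960 + 0.8416)² × (4.5/3.78)² = 22.2, so 23

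Thirty per arm in each of two strata gives 60 per group and 120 in total. The stated size therefore reproduces at 90% power, two-sided 5%, with the ICC left out.

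**2. Applying the ICC as a cluster design effect.** 1 + (30 − 1) × 0.2 = 6.8.

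- Required per arm: 29.8 × 6.8 = 203 (90%) or 22.2 × 6.8 = 151 (80%)
- Sixty per arm would be worth 60/6.8 = 8.8 women, with power of about 42%, or 38% (t), for 3.78

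Used this way, the ICC cannot lead to 60 per group.

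**3. Power if the between-arm effect is smaller than 3.78.** SD 4.5. Half of 3.78 is an illustration only.

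| Between-arm difference | 60 v 60 overall | 30 v 30 in one stratum |
|---|---|---|
| 3.78 | 99.5% (t) | 89% (t) |
| 1.89 | 63% | 36% (t) |

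**4. The parity interaction.** With 30 per cell, SE = SD × √(4/30) = 4.5 × 0.365 = 1.64.

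- Interaction of 3.78: 3.78/1.64 − 1.96 = 0.34, power 63%
- Interaction of 1.89: 1.89/1.64 − 1.96 = −0.81, power 21%
- Cell size for 80% power at 3.78: 4 × (1.960 + 0.8416)² × (4.5/3.78)² = 44.5, so 45 per cell (180 in total)

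**5. Which SD.** As written, 4.5 reads as the SD of the before-after change. If so, and if the SDs at the two visits are equal with pre-post correlation r, the residual SD for ANCOVA adjusted for pretest is 4.5 × √((1 + r)/2). For r = 0.2, 0.5 and 0.7 (assumed) this is 3.49, 3.90 and 4.15.

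Detectable differences at 80% power are 2.80 × SD × √(2/60) overall, √(2/30) within a stratum and √(4/30) for the interaction:

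| SD | Overall | Within stratum | Interaction |
|---|---|---|---|
| 4.5 | 2.3 | 3.3 | 4.6 |
| 3.49 to 4.15 | 1.8 to 2.1 | 2.5 to 3.0 | 3.6 to 4.2 |

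With the smaller SDs, overall power for 1.89 is 70% to 84%. Interaction power is 70% to 84% for 3.78 and 24% to 32% for 1.89.

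**The case against.** The strongest reply is that the arithmetic is sound: the plain formula gives 60 per group, and the primary comparison is well powered for the planning effect. Both statements are right. A reader might infer from the unused ICC that the 60 cannot be reproduced. It can, provided the unstated 90% and two-sided 5% are accepted. The 38% to 42% power in step 2 shows only that the ICC and the stated size do not belong together; it is not the power of this trial.

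A second reply is that 0.2 might be a correlation between repeated scores. A factor of 1 − 0.2² gives 29.8 × 0.96 = 28.6, or 29 per cell, close to the stated 30. But the text calls it an intraclass correlation and speaks of clusters, so it needs rewording on this reading too.

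A third reply concerns the SD. ANCOVA on the pretest is at least as efficient as analysis of change, so figures based on 4.5 may be pessimistic. This stands, and is why ranges are given. It helps the interaction test least where it matters: power for 1.89 stays at or below about 32%.

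Finally, it is tempting to call 3.78 an upper bound for the treatment effect. The article gives no course of scores under usual care. If control scores fell, the between-arm difference could exceed 3.78. What can be said is that it is uncontrolled and may overstate the effect.

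**Conclusion.** The point holds as a fault in the stated basis of the sample size, not in its arithmetic. A change over time stands in for the between-arm difference, and the ICC neither applies to individual randomization nor contributed to the 60 as a design effect.

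The parity-power claim is true only in a narrow sense: about 89% within a stratum at SD 4.5, if all of the 3.78 is treatment effect. For the interaction, which is the stated objective, power at SD 4.5 is about 63% for 3.78 points and 21% for 1.89. Under the assumed ANCOVA SDs, it passes 80% for 3.78 only at the most favourable correlation tried.

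A reader might infer that the primary comparison is underpowered. The documents do not show that: 60 analysed per arm detects about 1.8 to 2.3 points at 80% power, and no between-arm effect is given against which to judge this.

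These figures rest on two-sided 5% testing, 60 analysed per arm split 30 and 30 by parity, and the SD assumptions shown.

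**What to change.** Rewrite the Sample Size paragraph:

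- Delete the ICC and the cluster wording, and describe an individually randomized two-arm comparison stratified by parity.
- State that 3.78 is an uncontrolled before-after change, which may differ from the between-arm effect and may overstate it.
- State the power and sidedness used, and say whether 4.5 is the SD of the change or of the score.
- Report the detectable differences at 80% power, two-sided 5%, with 60 analysed per arm: about 2.3 points overall, 3.3 within a stratum and 4.6 for the interaction at SD 4.5; or about 1.8 to 2.1, 2.5 to 3.0 and 3.6 to 4.2 if 4.5 is the change-score SD and the pre-post correlation is 0.2 to 0.7.
- Replace the parity-power claim with two statements: within-stratum power depends on the 3.78 assumption; and the interaction test has low power, so a non-significant result does not confirm the hypothesis of no difference by parity.

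The cost is one rewritten paragraph and a less favourable power statement. No participants are added, and allocation, outcomes and tests stay as they are. The article reports recruitment as still under way, so this can be done before results are interpreted.

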### Screening and Baseline

Interested participants will contact the research team via text message to complete the automatic remote eligibility screening process. All participants will receive a welcome message as well as details about the study and what the study will entail. During the antenatal recruitment process, the woman’s phone number, first name, and due date will be collected via TextIt [30]. This information is required to ensure that follow-up messages are sent to the woman via her mobile device based on her due date.

During the antenatal screening process, participants will be screened for eligibility, and eligible participants will be informed of the need to send a text within 10 days after giving birth to be enrolled in the study. Women who have not yet given birth are sent messages at 39 weeks, 40 weeks, 41 weeks, and 42 weeks or until enrolled or withdrawn to remind them of the need to text the word “delivered” after giving birth. Participants who initiate contact before 37 weeks will be asked if they want to be sent follow-up messages once they reach 37 weeks until the sample size is reached.

Once a woman gives birth or enrolls after giving birth, she will be asked screening questions to ensure eligibility and determine parity for stratification. Additional details including the newborn’s name, preferred gender pronoun for the infant, infant’s date of birth, and parity will be collected at that time. Once stratified, participants will be randomized and informed of their group allocation. Participants who are randomized to the intervention group will be asked their preference on breastfeeding and formula feeding messages. All participants will be asked to complete the consent form and baseline survey. To remind participants to complete the survey, reminder text messages will be sent via TextIt every other day for 2 weeks (a maximum of 6 total messages) or until the survey is completed. An email will be sent as a final reminder to participants who have not yet completed the survey after day 14. If an email address was not provided, an expanded text message will be sent on day 14 instead. Participants will also be informed that they may message “STOP” to withdraw from the study at any time. If a participant withdraws from the study, they will not receive any further messages nor will they be asked to complete any future surveys. Participants who complete the baseline survey will receive an electronic gift card worth Can $15 (US $11.97).

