### Randomization

Using a 1:1 allocation, participants will be randomized into either the intervention group or the control group using the “split randomly” function within the TextIt platform [30]. This function randomly passes contacts through approximately equally distributed pathways in the flow and will allocate them to receive either the intervention or the control condition. Randomization will occur after a participant has given birth. Participants will be stratified into 2 groups based on parity (primiparous and multiparous) prior to randomization.

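### Parity-level power rests on 30 women per parity-by-arm cell, but only a total of 140 is fixed, so the claim holds only under a roughly even parity mix that the article neither states nor secures

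*Protocol article*

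**What the plan says.** The Sample Size section takes the feasibility study's baseline-to-6-week change of 3.78 (SD 4.5) and, "with stratification by parity and a moderate intraclass correlation of ρ=0.2", concludes that "a sample size of 30 participants per cluster and 60 participants per group (120 total participants) is required to be powered for analysis at the" parity level. Sixty per group at 30 per cluster means two clusters in each arm. These can only be the two parity strata, so the design has four parity-by-arm cells, the same four groups that the Data Analysis section compares.

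For attrition, "the estimated sample size will be increased by 15% to 69 participants per group, rounded up to 70 participants". The section ends with one enrolment figure: "In total, 140 participants will be enrolled in the study".

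The Randomization section gives parity one role: "Participants will be stratified into 2 groups based on parity (primiparous and multiparous) prior to randomization". Under Screening and Baseline, women who make contact before 37 weeks may be "sent follow-up messages once they reach 37 weeks until the sample size is reached"; this too refers to a single sample size. The Inclusion Criteria and Recruitment sections accept women of any parity. The article states no target, cap or expected proportion for either parity group.

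**The concern.** A requirement of 30 per cell describes 60 first-time and 60 experienced mothers with usable data. An overall total of 140 delivers that only if the women who enrol happen to divide about evenly. Stratified randomization does not help: even perfect blocking within parity leaves the number of women in each stratum to chance and to whoever responds to the advertising. This is therefore a separate matter from how the messaging platform allocates women.

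What is at stake is the parity question: the second secondary objective, and the stratified results named in the abstract. The matching hypothesis is that parity makes no difference. If one stratum is thinner than planned, its own effect is estimated less precisely, and a non-significant result is easier to misread as support for that hypothesis.

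**Working it through.** **Inputs.** From Sample Size: 30 per cell, 60 per group, 120 in total; 15% inflation; 15.5% incompletion in the feasibility study; 140 enrolled; effect 3.78, SD 4.5. From Randomization: 1:1 allocation. From Data Analysis: significance level 0.05 (taken as two-sided), and women lost to follow-up are left out, so completers are what count. Assumed, because the article does not give it: the parity mix, varied from 50:50 to 70:30.

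**Reproducing the plan's figures.** 30 × 4 = 120. 60 × 1.15 = 69, rounded to 70 per group, and 2 × 70 = 140. This agrees.

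No power level is stated. For a two-sided comparison of two means, the normal approximation n = 2 × [(1.96 + z) × 4.5 / 3.78]² gives 23 per arm at 80% power, 26 at 85%, 30 at 90% and 37 at 95%. So 30 per cell matches about 90% power for the arm difference inside one parity stratum, with the intraclass correlation left out. With the usual design effect, 1 + 29 × 0.2 = 6.8, it does not reproduce.

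**Completers per cell in the smaller stratum.** With p the smaller stratum's share, n = 140 × p × 0.845 / 2.

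**Power in that stratum.** Φ(0.84 × √(n/2) − 1.96), where 0.84 = 3.78 / 4.5. At n = 30 this is 90.2%.

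**Standard errors relative to an even mix.** For the arm difference in the smaller stratum the ratio is √(0.5/p). For the arm-by-parity contrast, whose variance is proportional to 1/p + 1/(1 − p), it is √{[1/p + 1/(1 − p)] / 4}.

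| Mix | Completers per cell, smaller stratum | Power in that stratum | SE rise, smaller stratum | SE rise, arm-by-parity contrast |
|---|---|---|---|---|
| 50:50 | 29.6 | 89.8% | 0 | 0 |
| 55:45 | 26.6 | 86.5% | 5% | 0.5% |
| 60:40 | 23.7 | 82.4% | 12% | 2% |
| 65:35 | 20.7 | 77.1% | 20% | 5% |
| 70:30 | 17.7 | 70.6% | 29% | 9% |

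**Share needed for 30 completers per cell.** 60 / (140 × 0.845) = 50.7%, which a smaller stratum cannot reach. With no loss at all it is 60 / 140 = 42.9%.

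**Separating two causes.** The step from 30 to 29.6 at an even mix does not come from parity. It arises because the size was multiplied by 1.15 instead of divided by 0.845 (60 / 0.845 = 71.0, so 72 per group for whole cells of 36). Everything below 29.6 comes from the mix.

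**The case against.** The strongest reply concerns size. The parity objective asks whether the effect differs by parity, so the contrast of interest is arm by parity. There the larger stratum gains much of what the smaller one loses, and the standard error rises by only 2% at 60:40 and 9% at 70:30. That stands. A reader might carry the 12% or 20% rise inside the smaller stratum over to the parity test, or conclude that the trial cannot address parity; the arithmetic supports neither.

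Second, fewer than 30 is not the same as underpowered. The article names no power level, and 23 per cell would give 80% on its effect and SD. At 60:40 the smaller stratum is still at about 82%, and it drops below 80% only nearer 65:35. This also stands, with the caution that all these power figures rest on a large effect taken from a pre-post change.

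Third, nothing in the documents shows that the mix will be uneven, and the phrase about the sample size being reached concerns messages to early contacts, so it is not a closure rule. An article may also leave recruitment targets by stratum to the full protocol. These points rule out saying that the smaller stratum will fall well short, or that a quota is missing. They do not rescue the sentence in the article, which asserts parity-level power without the condition it depends on.

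Finally, stratified randomization without quotas is common, and a cap would turn away eligible women. That is a fair reason not to insist on one.

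**Conclusion.** The point holds as a conditional claim stated unconditionally. The article ties parity-level power to 30 women per cell, and the enrolment rule it gives does not secure that number. At its own 15.5% loss, 140 women give 29.6 completers per cell at best, and fewer in the smaller stratum under any uneven mix. Power within that stratum would be about 82% at 60:40, 77% at 65:35 and 71% at 70:30, against about 90% at 30 per cell. The precision of the arm-by-parity contrast suffers much less.

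These figures assume exact 1:1 allocation within strata, equal loss in all cells, a two-sided 0.05 test, the normal approximation, the planning effect of 3.78 (SD 4.5) and the stated mixes, which are illustrative. The direction does not depend on any one mix.

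A reader might infer that the primary comparison is weakened as well. It is not: self-efficacy is compared between all women in each arm, whatever their parity. The matter is confined to a secondary objective and to how its result is read.

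**What to change.** In the Sample Size section, state that 30 per cell, and with it the parity-level power, holds only under a roughly 50:50 parity mix. Name the power level, and give the power within the smaller stratum over a range of mixes, as in the table above. In the Data Analysis section, commit to reporting the effect in each parity group and the arm-by-parity contrast with confidence intervals, and say that a non-significant contrast will not be read as showing no difference by parity. This costs a few sentences and changes nothing in the conduct of the trial.

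Optionally, if the claim is to stand without a condition, set an enrolment target for each parity stratum in the automated screen, where parity is already asked before randomization. The target would be 72 per stratum: 30 / 0.845 = 35.5, so 36 per cell, 72 per stratum and 144 in total. A target of 70 would again give only 29.6 completers per cell. Asking parity at the antenatal screen as well would avoid refusing women only after birth. The price is longer recruitment in the scarcer group and some eligible women turned away. Without a cap, keeping 30 completers per cell would need a total of about 158 at a 45% share, 178 at 40%, 203 at 35% and 237 at 30% (60 / (p × 0.845), rounded up).

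### Attrition is allowed for by multiplying by 1.15 rather than dividing by 0.845, so 140 enrolled are expected to give about 118 completers, slightly fewer than the 120 required

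*Protocol article*

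**What the plan says.** The Sample Size section of the protocol article first sets the number needed, with the parity strata in mind: "a sample size of 30 participants per cluster and 60 participants per group (120 total participants) is required to be powered for analysis". The loss rate comes from the team's earlier study and is applied in a single step: "there was an incompletion rate of 15.5%; thus, the estimated sample size will be increased by 15% to 69 participants per group". The 69 is then taken to 70. The section ends with the enrolment target: "In total, 140 participants will be enrolled in the study".

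Two other sections bear on this. Under Randomization, the allocation is equal: "Using a 1:1 allocation, participants will be randomized into either the intervention group or the control group". Under Data Analysis, the analysed population is formed by "excluding women who requested to stop receiving the messages or were lost to follow-up", so each woman lost reduces the number analysed. The article states no other reserve against attrition.

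**The concern.** The allowance should turn a required number of completers into a number to enrol. If a fraction d of those enrolled is lost, the number to enrol is n/(1 - d). The section uses n x (1 + d) instead, which is always smaller, and it also takes d as 15% where the quoted rate is 15.5%. Because women lost to follow-up are left out of the analysis, the 120 must be met by women who complete.

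What is at stake is consistency. The section calls 120, 60 and 30 required, yet its own enrolment figure and loss rate do not deliver them in expectation. A trial report that repeats the justification would carry the mismatch forward.

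**Working it through.** **Inputs, all from the protocol article**
- Required for analysis: 30 per cell, 60 per group, 120 in total (Sample Size).
- Incompletion rate: 15.5% in the feasibility study; 15% as applied (Sample Size).
- Allocation 1:1 (Randomization).
- Effect and SD: "mean difference in self-efficacy scores between baseline and 6-week follow-up of 3.78 (SD 4.5" (Sample Size).
- Significance level 0.05 (Data Analysis); taken as two-sided, which is an assumption.

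**Step 1: reproduce the stated figure.** 60 x 1.15 = 69.0, rounded to 70; 2 x 70 = 140. This matches exactly, so the method is clear. Using 15.5% in the same formula gives 60 x 1.155 = 69.3, which also rounds to 70. The rounding of the rate therefore does not change the total; the choice of formula does.

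**Step 2: inflate on the enrolled denominator, n/(1 - d).**

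| Loss rate | Per group | Rounded up | Total |
|---|---|---|---|
| 15% | 60/0.85 = 70.59 | 71 | 142 |
| 15.5% | 60/0.845 = 71.006 | 72 | 144 |

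At 15.5% the rounding is a close call, since 71 x 0.845 = 59.995. Rounding only the total gives 120/0.845 = 142.01, or 143. By cell, 30/0.845 = 35.5, or 36, which again gives 144. The stated 140 is thus 2 to 4 women short.

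**Step 3: what 140 enrolled is expected to give.**

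| Loss rate | Total | Per group | Per cell, equal strata |
|---|---|---|---|
| 15.5% | 140 x 0.845 = 118.3 | 70 x 0.845 = 59.15 | 35 x 0.845 = 29.6 |
| 15% | 140 x 0.85 = 119.0 | 70 x 0.85 = 59.5 | 35 x 0.85 = 29.75 |
| Required | 120 | 60 | 30 |

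Rounding 69 up to 70 narrows the gap but does not close it at either rate. If losses are independent at 15.5%, the binomial chance of at least 120 completers is about 40% from 140 enrolled and about 70% from 144.

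**Step 4: effect on power.** Normal approximation for two means: power = Φ(δ/(σ√(2/n)) - 1.96), with δ = 3.78 and σ = 4.5.
- Within one parity stratum: 90.2% at n = 30 per cell, 89.8% at n = 29.575.
- Overall: 99.6% at n = 60 per group, 99.5% at n = 59.15.

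The difference detectable with 80% power, (1.96 + 0.84) x 4.5 x √(2/n), moves from 3.26 to 3.28 points per stratum and from 2.30 to 2.32 overall. These figures only measure the change caused by the shortfall. The article states no power, the 3.78 is a before-after change rather than a difference between arms, and the intraclass correlation of 0.2 is not used here.

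**The case against.** The strongest reply is that nothing of consequence changes. The shortfall is 1.7 women in 120, or 0.85 per group and about 0.4 per cell. Power moves by less than half a point. The primary objective is the overall comparison of self-efficacy after the intervention, whereas the 30 per cell serves the parity question, which is secondary. All of this stands, and it is why the point is minor.

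A second reply is that the denominator of the 15.5% is not given; it lies in the feasibility study, which is not shown. That also stands as a caveat. A share of those who started is the natural meaning of an incompletion rate, but it is an assumption here. So is carrying that rate over to this trial, because the time point at which it was measured is not stated.

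A reader might infer something stronger: that the wrong formula leaves the trial underpowered, or leaves the parity cells far below 30. The documents do not support the first, as step 4 shows. The second confuses two issues. With an assumed 50% primiparous, an unrestricted random split and 15.5% loss, simulation puts the chance that all four cells reach 30 completers at about 0.6% with 140 enrolled, but still only about 2.5% with 144. That risk comes from the chance mix of parity and allocation, not from the inflation formula. The 50% is itself an assumption, since the article gives no parity split. Imbalance between cells is a separate matter that correcting the formula does not cure.

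**Conclusion.** The figure is wrong as written, by a small amount. On the section's own 15.5%, read as a share of those enrolled, 140 women are expected to yield about 118 completers (59 per group, 29.6 per cell with equal strata) against a stated requirement of 120, 60 and 30. At 15% loss the yield is 119, which is still short. The enrolment that meets 60 per group in expectation, with strict rounding up, is 144.

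The cost in power is under 0.5 percentage points on the plan's effect and SD, with a two-sided 0.05 test. The conclusion assumes that this trial's loss equals the feasibility rate and that the rate covers every woman the Data Analysis section would exclude. If women who only stop the messages are not counted in the 15.5%, the shortfall would be somewhat larger; the article does not say.

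**What to change.** Correct the attrition sentences in the Sample Size section. State that 140 enrolled are expected to give about 118 women with 6-week data (59 per group) at 15.5% loss, that 30 per parity cell is not assured, and that any power statement rests on 59 per group. Say also that the 15.5% is taken as a share of those enrolled. This needs no additional women.

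If the sponsor prefers to keep 120 as the requirement, the matching enrolment is 60/0.845, or 72 per group and 144 in total: four more women. That meets 120 in expectation only. It should not be described as securing 120 completers, or 30 in each parity cell.
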